## Methods

### Study design

The study has a pseudo-random, mixed-methods, pre-post design involving an intervention group of participants who completed a cooking program that consisted of a 1.5-h session once a week for 7 weeks, in eight locations throughout WA. There was also a control group that comprised participants from these locations who were on the program wait-list (Fig. 1).

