### Sample size

The sample size calculation in this study was based on the findings of the first published quantitative evaluation of Jamie’s Ministry of Food (JMOF) program into its impact on participants’ cooking confidence [42]. Flego et al. reported an increase of > 0.53 on a 5-point Likert scale across all confidence items, which corresponded to a large Cohen’s effect (d > 0.8), whilst no significant changes were observed in the Control group (all *p* > 0.13). Using G*Power, the required sample for a mixed-model analysis of variance test (ANOVA) design (2 groups, each with 2 time points) to detect (conservatively) a small-medium, within-between, interaction effect (Cohen’s *f* = 0.15), at the 5% level of significance and 80% power was 90, or 45 per group. However, Flego et al. [42] noted that the participant retention rate in the JMOF program at T2 was 55% (694 at T1 and 383 at T2). To account for this and to ensure sufficient participation numbers at the end of T2, the aim was to recruit a minimum of 164 participants with 87 in each time-point (i.e. T1 and T2) of the intervention arm. No power calculation to account for T3 samples size was conducted as the investigation was not aiming to detect a change, rather, whether the effect was maintained at T3.

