### Statistical methods

The computer software package IBM SPSS Statistics for Windows version 25.0 (Armonk, NY: IBM Corp) will be used to access the data set and perform the statistical analyses. For the basic online evaluation questionnaire, general descriptive analyses including frequency data with appropriate plots and cross-tabulations will be used to explore and summarise outcome variables. Continuous demographic and baseline characteristics will be summarised using standard statistics (mean and standard deviation) and non-parametric statistics (medians and inter-quartile ranges) where appropriate. Independent *t*-test for normally distributed data, and Mann-Whitney U test for non-normal data, will be used to assess differences between the groups. Frequencies and percentages will be reported for categorical variables and Chi-square test will be used to test for differences in proportion between the groups. The magnitude of change both within and between the intervention and control groups will be assessed using mixed-model ANOVA. Furthermore, changes within the intervention group will be assessed across three time points IT1, IT2 and IT3 using repeated-measures ANOVA. To account for multiple outcomes, the Benjamini-Hochberg correction (i.e. false discovery rate) will be applied to the raw *p*-values. Participants with missing value for the variables of interest (either outcome or predictor) will be removed from the repeated-measures ANOVA models. Specific demographic factors of interest (including but not limited to, gender, age, education, BMI and employment) will be adjusted for in all models. Statistical significance will be indicated at the 10, 5 and 1% level. Cohen’s effect sizes will be provided as a measure of practical/clinical significance and to assist in the interpretation of said ‘statistically significant’ results.

To interpret gut microbiota diversity and to analyse the microbial composition of the gut microbiota, multivariate analysis using a combination of R and PRIMER7 and Permanova+ (PRIMER-E, Plymouth) [82] will be conducted. Principal Coordinates Analysis (PCoA) will be deployed to visualise findings. Distance-based linear models (DISTLM) and distance-based redundancy analysis (dbRDA) will be used to integrate microbiome findings with other relevant data (i.e. dietary intake) that help explain the relationship between the microbiome findings and other outcomes.

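### With only 55% retention expected at T2, the stated missing-data rule deletes incomplete participants, and no analysis that keeps their data is named

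*Protocol article*

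**What the plan says.** The Sample size section of the protocol article requires 90 participants, "at the 5% level of significance and 80% power was 90, or 45 per group", for a mixed-model ANOVA with two groups and two time points. It notes that in the earlier evaluation the "participant retention rate in the JMOF program at T2 was 55% (694 at T1 and 383 at T2") and answers this by over-recruiting: "the aim was to recruit a minimum of 164 participants with 87 in each time-point (i.e. T1 and T2) of the intervention arm". For the six-month survey it states: "No power calculation to account for T3 samples size was conducted".

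The Statistical methods section names a mixed-model ANOVA for change within and between arms, and a repeated-measures ANOVA for IT1, IT2 and IT3 in the intervention arm. All models adjust for demographic factors that include gender, age, education, BMI and employment. The missing-data rule is: "Participants with missing value for the variables of interest (either outcome or predictor) will be removed from the repeated-measures ANOVA models". The article names no analysis that retains partial records and no sensitivity analysis for missing data.

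The intervention arm is described in two ways. Study design speaks of a design "involving an intervention group of participants who completed a cooking program". Assignment of groups instead places adults in an arm by the class day they chose, and sets no attendance or completion condition.

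**The concern.** Over-recruitment protects power. It does nothing about who is left when nearly half of those recruited are expected to be gone by T2. A rule that deletes everyone with a missing value gives an unbiased arm-by-time contrast only if loss is unrelated to outcome once the adjusted covariates are accounted for. In a voluntary program with a self-rated primary outcome that is a strong condition, and nothing in the plan tests it.

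The three-time-point model loses more. Its purpose is to see whether the effect is maintained, yet listwise deletion answers that only in people who returned the six-month survey, and ignores the observed IT1 and IT2 values of everyone else.

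The two descriptions of the intervention arm add an ambiguity. If completion of the program were used as a filter, it would be a post-baseline filter that controls, who are assessed before their own program starts, cannot face.

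**Working it through.** **The plan's own figures.** Inputs from the Sample size section: f = 0.15, two groups, two time points, 5% significance, 80% power. The correlation between time points is not given; 0.5 is assumed, which is the G*Power default.
- Noncentrality: λ = f² × N × m / (1 − ρ) = 0.0225 × 90 × 2 / 0.5 = 8.1, with 1 and 88 degrees of freedom. Power is 80.4%, so N = 90 reproduces. At ρ = 0.3 or 0.7 the required N would be 126 or 56.
- Planned effect in SDs of change: λ = N × δ² / 4, so δ = √(4 × 8.1 / 90) = 0.60.
- Retention: 383 / 694 = 55.2%. Inflation: 90 / 0.55 = 163.6, giving 164, which reproduces. The same calculation gives 45 / 0.55 = 81.8, or 82 per arm, so the 87 quoted for the intervention arm does not reproduce. It is not used here.

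**How many are dropped.**
- By T2: 164 × 0.55 ≈ 90 kept, so 164 − 90 = 74 (45%) removed. These people have a baseline survey but no T2 survey.
- Three-time-point model: 82 × 0.55 ≈ 45 at IT2. The article gives no IT2-to-IT3 retention. If it is 80%, 60% or 55% (assumed), about 36, 27 or 25 complete cases remain, and about 9, 18 or 20 people with valid IT1 and IT2 data are discarded.

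**How far the contrast could move.** Assume that change is normal, that 55% are observed, and that the log-odds of being observed are linear in a person's own change, in the intervention arm only. The intercept is solved to give 55%. The bias is the mean standardised change among those observed. The last column takes 45 completers per arm and no true effect.

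| Assumed odds ratio per SD of change | Bias, SD | Share of 0.60 SD | Rejection rate of the 5% test |
|---|---|---|---|
| 1.0 | 0 | 0% | 5% |
| 1.25 | 0.10 | 17% | 8% |
| 1.5 | 0.18 | 29% | 13% |
| 2.0 | 0.28 | 47% | 26% |

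**What a mixed model recovers.** In the same scenario (ρ = 0.5 assumed), likelihood estimation on all observed T1 and T2 data leaves 0.08, 0.13 and 0.22 SD at odds ratios 1.25, 1.5 and 2.0. About three quarters of the bias remains, because selection on own change is not missing at random.

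**The case against.** Several stronger readings are tempting, and the article does not support them.

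- *The plan defines the intervention arm as completers.* A reader might infer this from Study design. The operative definition is in Assignment of groups, by class day and without a completion condition, and Statistical methods names no completer population. The two sections need reconciling; no more than that follows.
- *Only the intervention arm is filtered.* The deletion rule applies to anyone with a missing value, so controls lacking CT2 or a covariate go too, and the 55% was applied to the total of both arms. An asymmetry would need completion to be used as a filter, or dropout that is driven by the program.
- *The bias favours the program.* It is plausible that people who gained less leave more often, but the article has no data on this. The bias is zero if loss is unrelated to change, and it cancels in the contrast if both arms select alike.
- *T2 data are thrown away for nearly half the sample.* Those lost by T2 have none. Only their baseline is discarded. Observed T2 data are lost only through a missing covariate or, in the three-time-point model, a missing IT3.
- *Deletion is valid only under completely random loss.* That is too strict: loss that depends only on covariates in the model is also tolerable.

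A fair point on scope also stands. The rule names the repeated-measures ANOVA models, and the between-arm test is called a mixed-model ANOVA. The article does not spell out whether the rule covers it. A two-time-point mixed ANOVA is nevertheless itself a repeated-measures design, and in its usual form it needs both time points from each participant.

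Finally, the mixed model alone does not cure the scenario quantified above. That is correct, and it is why the sensitivity analysis is an essential part of the fix.

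**Conclusion.** The point holds as a weakness in a stated rule. It is not merely a gap left to another document. Loss of 45% by T2 is expected, it is met by over-recruitment alone, and incomplete participants are then deleted with no named alternative. The potential error in the arm contrast is 0 to 0.28 SD, up to 47% of the planned 0.60 SD. That range rests on four assumptions: odds ratios of 1.0 to 2.0 per SD of change, selection in the intervention arm only, 55% retention as in the earlier evaluation, and a correlation of 0.5 for the 0.60 SD benchmark. The article shows neither the size nor the direction of any such selection. The improvement is worth making because it is cheap, not because bias has been demonstrated.

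**What to change.** 1. State that the analysis set is all consenting participants with a baseline survey, in the arm given by class day under Assignment of groups, whatever their attendance. Align the Study design wording with this.
2. Replace listwise ANOVA with a likelihood-based linear mixed model (arm, time, arm × time, unstructured covariance, the planned covariates) on all available observations for the between-arm comparison. Use the corresponding model, with time alone, for IT1-IT3.
3. Impute missing covariates rather than deleting those participants.
4. Add a delta-adjusted sensitivity analysis in which intervention dropouts are taken to change like controls. It tests the missing-at-random assumption and does not remove the bias: with no true effect and a bias of 0.28 SD among those observed, it would still give 0.55 × 0.28 ≈ 0.15 SD.
5. Keep the complete-case analysis as secondary.

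No new data are needed, SPSS can fit the mixed model, and the analyses are written in the future tense. The cost is a little more analysis work and a possibly smaller estimated effect.

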### Primary and secondary outcomes and endpoints

The primary outcome of cooking confidence was evaluated via the theoretical concept of personal beliefs of self-efficacy measured across five areas:
Confidence about being able to cook from basic ingredients;Confidence about following a simple recipe;Confidence about preparing and cooking new foods and recipes;Confidence that what is cooked will “turn out” well; andConfidence about tasting foods not eaten before.

This was performed using the same method as described by Flego et al. [42] by measuring cooking confidence as a proxy for self-efficacy. The questions used were based on works by Short (2003) and Barton (2011) and presented on a 5-point Likert confidence scale ranging from ‘not at all’ to extremely’ confident. This was explored in terms of change over time and between different study groups.

The secondary endpoints were measures of dietary intake, physical activity and mobility levels, body composition, anthropometry, blood, urine and faecal biomarkers of systemic, physical and mental health and are further explained in the sections below. These were also explored in terms of change over time and between different study groups.

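### Significance is to be flagged at 10%, 5% and 1% with no deciding level, although the study is sized for one test at 5%; the false-discovery family for the five confidence items is also not stated

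*Protocol article*

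**What the plan says.** All of this is in the Methods of the protocol article.

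- **Sample size.** The calculation is for a "mixed-model analysis of variance test (ANOVA) design (2 groups, each with 2 time points"), with an interaction effect of Cohen's f = 0.15. The required number "at the 5% level of significance and 80% power was 90, or 45 per group". The recruitment target of 164 follows from 55% retention at T2.
- **Primary and secondary outcomes and endpoints.** The primary outcome is cooking confidence, "measured across five areas", each rated on a 5-point scale. The article defines no summary score and no lead item.
- **Statistical methods, multiplicity.** "To account for multiple outcomes, the Benjamini-Hochberg correction (i.e. false discovery rate) will be applied to the raw" p-values. No false-discovery level is given, and nothing says which outcomes form the family.
- **Statistical methods, significance.** "Statistical significance will be indicated at the 10, 5 and 1% level". The sentence after it offers effect sizes to help interpret results that have been called significant, so the 10% flag carries that label.

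**The concern.** The design rule and the analysis rule differ. The sample size fixes 5% for one interaction test. The analysis section allows three levels without ranking them, and the loosest is twice the design level. A confidence item with an adjusted p-value of 0.08 could be reported as a significant improvement under the text as it stands. It could equally be reported as not significant by appeal to the Sample size section.

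The multiplicity sentence leaves a second choice open. Benjamini-Hochberg thresholds depend on how many outcomes are ranked together and how many of the others have small p-values. The secondary list is long: energy and 31 nutrients, several questionnaires, clinic measures, and blood, urine and stool markers. If the five primary items were ranked with these, the verdict on cooking confidence would depend partly on results that have nothing to do with it. If they were ranked alone, it would not.

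What is at stake is whether the statement that the program improved cooking confidence has an error rate known in advance.

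**Working it through.** **Inputs.** From Sample size: f = 0.15, two groups, two time points, 5% level, 80% power, N = 90, retention 55%. From Primary and secondary outcomes: five items. From Statistical methods: Benjamini-Hochberg, and levels of 10%, 5% and 1%. Assumed, because the article does not give them: correlation of 0.5 between the two time points; 20 secondary outcomes, independent of each other; and a shift of 4 standard errors in any secondary outcome that truly changes. Correlation between the primary items was taken as 0 and as 0.5.

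**1. The plan's own figure.** For the interaction, the noncentrality is f² × N × m / (1 − ρ) = 0.0225 × 90 × 2 / 0.5 = 8.1, on 1 and 88 degrees of freedom. At 5% the power is 80.4%, and 90 is the smallest even N that reaches 80%. Then 90 / 0.55 = 163.6, rounded up to 164. Both stated numbers reproduce, and they belong to a single test at 5%. With a correlation of 0, 0.3 or 0.7 the required N would be 178, 126 or 56, so 0.5 is very likely the value used.

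**2. The same test at the three levels, N = 90.**

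| Level | Power | N for 80% power |
|---|---|---|
| 10% | 88.1% | 72 |
| 5% | 80.4% | 90 |
| 1% | 58.6% | 134 |

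The stated 80% power holds at only one of the three.

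**3. Five null items as their own family.** With independent items, the chance that Benjamini-Hochberg at level q rejects anything equals q. Simulation (40,000 runs) gave about 10%, 5% and 1%; with item correlation 0.5 it gave about 8.8%, 4.5% and 1.0%. The primary error rate is therefore whichever level is read, and reading at 10% doubles the design rate.

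**4. Five null items pooled with 20 secondary outcomes, q = 5%.**

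- All 20 secondaries null: the whole family of 25 has a 5% chance of any rejection, and 5 of the 25 are primary, so roughly 5% × 5/25 = 1%. Simulated: 1.1%.
- 10 truly changed: a first null item is rejected at about 0.05 × 11/25 = 0.022, so 1 − 0.978⁵ = 10.5%. Simulated: 10.1%.
- All 20 truly changed: the threshold is about 0.05 × 21/25 = 0.042, so 1 − 0.958⁵ = 19.3%. Simulated: 18.9%, or 15.2% with item correlation 0.5.

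At q = 10% the three simulated values with independent items are 2.3%, 20.5% and 35.3%.

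**5. Power per primary item, all five at f = 0.15, N = 90, q = 5%.**

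- Own family: the threshold can rise to 0.05 × 5/5 = 0.05. Simulated power is 78.8% (independent items) or 76.8% (correlation 0.5).
- Pooled with 20 null secondaries: if only the five items are rejected, the threshold is at most 0.05 × 5/25 = 0.01. Simulated power is 54.8% or 54.3%.
- Pooled with 40 null secondaries: about 46%.

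**The case against.** Flagging several levels is a familiar table convention, and a reader could take 5% as implied by the sample size. The plan does correct for multiplicity. This is a condensed article, and the definition of the family may stand in an analysis plan that is not shown. Nor does the article say outright that the five items are tested separately.

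Most of this is fair, and it rules out several stronger readings that a reader might infer:

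- **That the plan pools primary and secondary outcomes.** It does not say so. It names no family, so pooling is one possible reading and the figures in step 4 show only what depends on the choice.
- **That the chance of a false primary claim is 41% at the 10% level (1 − 0.9⁵) or 23% at 5% (1 − 0.95⁵).** Those figures are for five independent, uncorrected tests. The plan corrects.
- **That doubling holds under any family.** Pooled with 20 null secondaries, the chance of a false primary claim at q = 10% is only 2.3%. The 10% figure applies when the five items stand alone.
- **That power falls to 59% because there are five items.** That is power at the strictest Benjamini-Hochberg step for five items, 0.01. It does not describe the case in which all five items shift, which is what the sample size takes from the earlier evaluation. There, power stays near 78%.
- **That the mean of the five items must become the primary outcome.** Its gain in power rests on inter-item correlations that the article does not give. Recruitment closed in November 2018, so the change would redefine the endpoint after recruitment had ended.

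The objection does not remove the wording on levels. Three unranked levels are stated in the text, and no sentence makes 5% decisive or the 10% flag merely descriptive.

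**Conclusion.** The point holds in a limited form. The article's stated rule lets a primary result be called significant at 10%, while the study was designed at 5%. With the five items corrected among themselves, that is about a 10% chance of any false claim when all are null, against 5%. This part rests on the text alone.

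The second part is an ambiguity: the family is not stated. Under the assumptions above, the choice moves the chance of a false primary claim between about 1% and 15-19% at q = 5%, and power per primary item between about 78% and about 54%. The count of 20 secondaries and the size of their effects are illustrative; other values change the numbers but not the dependence. If an existing analysis plan already separates the families, this part falls and the first remains.

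**What to change.** Amend the Statistical methods text, before the outcomes are analysed, to say that:

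1. the primary question is decided at two-sided 5% on the group-by-time interaction at T2;
2. the five confidence items form their own Benjamini-Hochberg family at 5%;
3. the secondary outcomes form a second, separate Benjamini-Hochberg family at 5%;
4. the 10% flag is dropped, and p-values are reported with confidence intervals.

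The mean of the five items may be added as a supportive analysis; it need not replace the primary outcome.

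The cost is wording only: no new data, no more participants and no change of endpoint. If all five items shift by the planned effect, power per item stays at about 77-79% with N = 90. The downside is that results between 5% and 10% can no longer be called significant. Benjamini-Hochberg still limits the expected share of false claims within the five items rather than the chance of any false claim once some items have truly changed, and the report should say so.

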## Discussion

It is well reported that an increased emphasis on families and individuals to change their dietary patterns and lifestyle can have significant impact on weight reduction and overall health [29, 83–87]. Family dinners are have been found to be a measurable signature of these social exchanges in the home that support socioemotional development and mental health [88]. A 2017 study reported an association between increased frequency of family dinners and lower rates of obesity that was pronounced for those whose meals were home-cooked [89]. Indeed, the consensus statement of the International Society for Nutritional Psychiatry Research (ISNPR) stresses the importance of diet and nutrition as a critical determinant of mental and physical health [90]. The collaboration of academics advocates for future public health interventions to stimulate a significant change in eating habits back to more traditional wholefood diets.

Yet, research in WA suggests that the demands on families [91–93], together with fatigue [93], lack of time, family/social support and overall motivation [91, 93, 94], impede prioritisation of a healthy diet and lifestyle [95].

The JMOF mobile kitchen has been delivering seven-week cooking programs to the community teaching basic cooking skills aimed at improving participants’ knowledge and ability to purchase, prepare and cook healthier meals at home. This study protocol describes the recruitment of willing participants and the assessment methods involved in an evaluation of the program’s effect on their cooking confidence, dietary intakes, physical and mental health and wellbeing. The study extends on previous, similar studies in that it includes collection and analysis of biomarkers of both metabolic and gut health. The study will provide valuable insight into the effectiveness of food literacy cooking programs and how improvements to cooking confidence and skills can contribute to healthier outcomes.

Strengths of the study include the extensive range of data collected that comprise; self-reported cooking confidence and self-efficacy and measures of physical and mental health and well-being. In addition, data has been collected on self-reported dietary intake; measures of health status from anthropometry, body composition, blood pressure, agility and grip strength, blood, urine and faecal biomarkers. The study has also collected longitudinal data to explore sustainability. Findings will support future public health cooking program initiatives aimed at improving food literacy, self-efficacy and physical and mental health. It is also novel in that it will help to identify mechanistic associations between dietary intake and interactions between human gut microbiota, their metabolites and their interplay with host metabolism in both physiological and mental health.

There is burgeoning evidence reporting the beneficial associations between the human gut-microbiome and the key microbes and their metabolites that are associated with health [18, 19]. Diets higher in protein and fats and lacking in fermentable substrates for the production of beneficial SCFA have increasingly been linked to poorer physical and mental health outcomes [65, 96–98] and the presence of microbial profiles that are more often associated with disease [76]. The inclusion of faecal bile acid analysis will enable investigation of their role in human metabolism beyond their core function of assisting with dietary fat digestion and absorption. Faecal bile acid composition is of great interest when studying the role of diet and gut microbiota in health and disease, due to the bi-directional interplay between gut bacteria and bile acid and cholesterol metabolism that leads to implications on host physiology [76, 99].

The study is limited due to the confines of the study design that prevented true randomisation. According to the Stages of Change theory [100], as the study participants were selected from the wait-list and had already committed to the program, they would have transitioned from the pre-contemplation to the change/action stage. Therefore the act of registering for the program could potentially instigate behaviour change, which may result in positive change within both groups [101]. As a consequence, the control group may not truly reflect the general population. The standard evaluation used the tool created for previous Australian cooking programs that were run in Victoria and NSW [42–44], however this study extended data collection to include more detailed assessments of physical and mental health as described in this protocol. The DQES vs 2 FFQ is a reflection of intake over 12 months, however it has been validated to detect change over a shorter timeframe in similar studies [58, 59].

The study’s strengths include the extensive data collected that will provide valuable insight to the effects that a basic cooking program incur within a healthy population of Australian adults. Findings will inform on the complex interaction between self-efficacy, dietary intake, gut-microbiota and biomarkers of physiological health and well-being, that may support the employment of basic cooking programs as a tool for future health promotion interventions.

